#### 3.2 Secondary Objectives

The secondary objectives are (1) to assess blinding success in outcome assessors of the study, (2) to identify factors contributing to perceived intervention arm allocation in study participants as well as outcome assessors, and (3) to explore the effect of two applied interventions on low back function.

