### **5.3.1 Randomization**

Stratified randomization (1:1 allocation ratio) will be performed using previous experience with MT (yes/no) as the stratification variable. This will be done, as we assume this characteristic may play a role when it comes to perceptions about assigned intervention. Varying permuted blocks (block sizes not disclosed to ensure allocation concealment) will be generated by an external biostatistician, and concealment of the list will be achieved electronically in REDCap.

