| Exclusion criterion: pregnancy or breastfeeding                                      | I am currently pregnant or breastfeeding.                                                                          | y/n                  |                 | x              |                |
| Self-reported back function assessment                                               | How would you rate your back flexibility at the moment?                                                            | 5-point Likert scale |                 | x              | x              |
|                                                                                             | Do you currently experience ache, pain, or discomfort in your upper back?                                          | y/n                  |                 | x              | x              |
|                                                                                             | If yes: How uncomfortable do you feel with the ache, pain, or discomfort in your upper back?                       | 3-point scale        |                 | x              | x              |
|                                                                                             | Do you currently experience ache, pain, or discomfort in your lower back?                                          | y/n                  |                 | x              | x              |
|                                                                                             | If yes: How uncomfortable do you feel with the ache, pain, or discomfort in your lower back?                       | 3-point scale        |                 | x              | x              |
| Thoracolumbar spine flexion–extension                                                | Thoracolumbar angle (Smartphone application)                                                                       | Degrees of motion    |                 | x              | x              |
| Blinding success in outcome assessors                                                | To which extent do you know which intervention (active intervention or control intervention) the patient received? | Blinding index       |                 |                | x              |

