## 8 STUDY PROCEDURES

### 8.1 Study Flow Chart/Table of Study Procedures and Assessments

This study consists of an online survey disseminated on November 7, 2022, (timepoint  $T_{-1}$ ), followed by an in-person visit taking place on November 8, 2022, during which either the active or control intervention will be administered (**Figure 1**).  $T_0$  specifies the pre-intervention period,  $T_1$  the post-intervention timepoint on the date of the in-person visit. Detailed decision guidelines are summarized in Figure 2.

In an introductory survey, study information will be provided and a number of characteristics will be recorded, such as the name, gender, year of birth, and previous experience with MT. In this same survey, the eligibility of the participants will be verified (**Table 1**).

On the day of the intervention, the intervention protocol, consisting of baseline measurement, application of active or control intervention, and outcome measurement will be performed. The process will take around ten minutes from  $T_0$  to  $T_1$ .

[figure not shown]

**Figure 1.** Study procedure of SENSATE: overview of the course of the trial.

[figure not shown]

**Figure 2.** SENSATE study flow.

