### Secondary Analyses

For our secondary analyses, we will quantitatively evaluate participant’s blinding with James’s BI. The range of this complementary index ranges from  $0$  (all correct) to  $1$  (all incorrect) and does not provide different values according to intervention. An index of  $0.5$  (half correct, half incorrect) indicates random guessing. In addition, we will also assess blinding index in the outcome assessors using Bang’s BI after completing and documenting measurements at  $T_1$ .

Both blinding indices (Bang and James) will be calculated with the R package {BI} based on the participant responses about their degree of confidence in their assigned intervention group (displayed in 5-point Likert scale format).

In the secondary analysis, the measured change in ROM (maximum flexion and extension) of the thoracolumbar spine will be compared within and between the intervention groups (active vs. control;  $T_0$  vs.  $T_1$ ), although formal statistical testing of difference between groups will not be performed, as this would not align with our primary objective. In case a large difference in baseline characteristics is detected between the groups, regression analysis with adjustment of anticipated confounders (i.e., age, gender, experience with MT, care-seeking history for LBP) may be considered.

Contributing factors to perceived intervention arm allocation in study participants, as well as outcome assessors, will be qualitatively analyzed using thematic analysis. Two study investigators will collate collected responses, group them thematically and develop emerging clusters using a consensus-based approach.

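### Covariate adjustment of the exploratory ROM comparison hangs on an undefined baseline imbalance and leaves out T0 ROM as a covariate; one listed covariate has no documented source

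*Protocol*

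**What the plan says.** Secondary objective 3 (protocol section 3.2) is "to explore the effect of two applied interventions on low back function". Under Secondary Analyses in section 10.2, "the measured change in ROM (maximum flexion and extension) of the thoracolumbar spine will be compared within and between the intervention groups". The plan then limits this comparison: "although formal statistical testing of difference between groups will not be performed".

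The adjustment rule follows in the same paragraph: "In case a large difference in baseline characteristics is detected between the groups, regression analysis with adjustment of anticipated confounders". The sentence goes on to name four covariates and how firmly the plan commits to them: "i.e., age, gender, experience with MT, care-seeking history for LBP) may be considered". What counts as a large difference is not defined, and T0 ROM is not in the covariate list.

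Three other places bear on this rule:

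- Table 1 (section 7.3) marks the ROM measure, "Thoracolumbar angle (Smartphone application"), at both T0 and T1.
- Section 5.3.1 randomises "using previous experience with MT (yes/no) as the stratification variable".
- Section 8.1 describes the intake survey as recording characteristics "such as the name, gender, year of birth, and previous experience with MT". Neither that sentence nor any item in Table 1 mentions care-seeking for low back pain.

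Section 5.3 commits the trial to the predefined analysis plan in section 10. The rule is therefore the stated plan, not a placeholder for detail to come.

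**The concern.** In a randomised trial, adjustment chosen after looking at baseline balance makes the reported estimate depend on the data. Here there are two discretionary steps: whether a difference counts as large, and whether the regression is then run.

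The model behind the trigger is also poorly matched to the outcome. If the imbalance were in T0 ROM itself, none of the four listed covariates would address it. The stratification factor is the covariate least likely to look imbalanced, because the design balances it, yet it enters only through this route. A fourth covariate has no described source.

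At stake is how readable and how precise the ROM part of secondary objective 3 is. The blinding results are not touched.

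**Working it through.** **Inputs.** From the protocol: 26 participants, 1:1 allocation (so 13 per arm), ROM at T0 and T1, change as the planned outcome, MT experience as stratification factor. Not in the protocol: any SD or T0–T1 correlation ρ for ROM, or any cut-off for a large difference. These are assumptions below, shown over a range. Equal variance at T0 and T1 is also assumed.

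**The plan's own figure.** The only stated precision is ±0.315 for the group-specific Bang index. Taking the cited method to be the worst-case multinomial formula (the equation is not printed), z(1−0.05/6)² × (1/3)(2/3) = 1.274, and √(1.274/13) = 0.313. The figure reproduces, but says nothing about ROM.

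**1. How often the trigger could fire by chance.** By simulation at 13 per arm, a single continuous covariate exceeds an absolute standardised difference of 0.2, 0.5 or 0.8 with probability p = 0.613, 0.212 or 0.052. Three listed covariates are not balanced by stratification (age, gender, care-seeking history). Treating them as independent and continuous, the chance that at least one exceeds the cut-off is 1−(1−p)³:

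| Assumed cut-off | One covariate | At least one of three |
|---|---|---|
| 0.2 | 61% | 94% |
| 0.5 | 21% | 51% |
| 0.8 | 5% | 15% |

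Whether the trigger fires depends largely on the undefined word.

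**2. Conditional bias of the change score.** Given an observed baseline difference Δ between arms, the expected between-arm difference in change is the true effect plus ρΔ − Δ, a bias of −(1−ρ)Δ. For Δ = 0.5 SD, its size is 0.5 × 0.5 = 0.25 SD at ρ = 0.5, 0.3 × 0.5 = 0.15 SD at ρ = 0.7, and 0.1 × 0.5 = 0.05 SD at ρ = 0.9. Averaged over randomisations it is zero. A model with T0 ROM as covariate removes it for the allocation actually obtained.

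**3. Precision.** In units of the ROM variance, the change score has variance 2(1−ρ) and the baseline-adjusted estimate 1−ρ². The ratio is (1+ρ)/2. Estimating one covariate slope at N = 26 multiplies this by (N−3)/(N−4) = 23/22 = 1.045.

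| Assumed ρ | (1+ρ)/2 | × 23/22 | Square root (SE ratio) | CI narrower by about |
|---|---|---|---|---|
| 0.5 | 0.75 | 0.784 | 0.885 | 11% |
| 0.7 | 0.85 | 0.889 | 0.943 | 6% |
| 0.8 | 0.90 | 0.941 | 0.970 | 3% |
| 0.9 | 0.95 | 0.993 | 0.997 | 0.3% |
| 0.95 | 0.975 | 1.019 | 1.010 | 1% wider |

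Break-even is where (1+ρ)/2 = 22/23, so ρ = 21/23 = 0.91. Simulation gave variance ratios of 0.793, 0.890, 0.997 and 1.023 at ρ = 0.5, 0.7, 0.9 and 0.95, in agreement. The table ignores the slightly larger t quantile.

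The MT-experience term costs one further degree of freedom. If it predicted nothing and stratification did nothing to balance it, the multiplier would be 23/21 = 1.095 and break-even 19/23 = 0.83. Stratified blocks make the real cost smaller.

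**4. The listed fallback.** Four covariates unrelated to ROM change would multiply the variance of the change contrast by 23/19 = 1.21, about 21% more.

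**5. Covariates against data items.** Age follows from year of birth, and gender and MT experience are in section 8.1. For care-seeking history, the nearest Table 1 item asks whether the participant ever received professional manual therapy for musculoskeletal disability. That is not specific to low back pain, does not cover care-seeking in general, and overlaps with MT experience, already listed.

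**The case against.** Several stronger readings are tempting, and the protocol does not support them.

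- *That baseline ROM is ignored.* It is not: the planned outcome is change from T0. It is absent only as a covariate.
- *That precision is lost for good.* T0 and T1 ROM are both recorded, so an adjusted estimate can be produced at any time. What would be lost is pre-specification.
- *That the comparison is biased or its error rate inflated.* The change score is unbiased over randomisations, no between-group test is planned, the trigger looks at baseline and not at results, and section 10.2 has the analysis done with masked arm labels.
- *That the listed model cannot be fitted.* The list in section 8.1 is open-ended and the demographics row of Table 1 is not itemised. The item may be on the survey, but it is not documented.
- *That secondary objective 3 rests on ROM alone.* Self-reported flexibility and upper and lower back discomfort are also measured at T0 and T1.

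The precision argument is also conditional. T0 to T1 takes around ten minutes, with the same application and procedure, so a high ρ is plausible and the gain may be negligible. Stratification already keeps MT experience roughly balanced, so omitting it from a descriptive contrast costs little.

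All of this limits the size of the point. It does not rescue an undefined trigger attached to a model without T0 ROM, or supply the missing source for one covariate.

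**Conclusion.** The concern holds as a minor point. Section 10.2 fixes the ROM adjustment badly in four respects: the trigger is undefined and optional, T0 ROM is not a covariate, the stratification factor enters only through the trigger, and care-seeking history for low back pain is not documented as collected.

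The textual findings rest on no assumption. The size does. The gain from adjusting for T0 ROM ranges from about 11% of interval width to nothing as ρ goes from 0.5 to about 0.91, and the protocol gives no ρ. The case for fixing one model in advance does not depend on ρ. Severity stays low because the outcome is exploratory and untested and the Bang index is unaffected.

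**What to change.** In section 10.2, delete the imbalance-triggered sentence and state: *T1 flexion and extension ROM will each be estimated by a linear model with arm, T0 ROM and MT experience, reporting the adjusted between-arm difference and 95% CI without a hypothesis test.* Within-arm change from T0 to T1 can stay as a descriptive summary.

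Either drop care-seeking history for low back pain from the covariates or, if it is wanted, add the item to Table 1 and section 8.1.

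The cost is about two sentences. Arm, T0 ROM and MT experience are already collected, and the decision not to test is kept. The downside is a small loss of degrees of freedom, which would make the interval marginally wider than the change score's if ρ is very high.

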## 10.3 Handling of Missing Data and Drop-Outs

Due to piloted results and data monitoring processes, missing data is unlikely in our study. Data missingness will be further prevented by maintaining active communication channels with study participants before and after enrollment in the study. However, due to our overemphasized small sample size, missing data in quantitative variables will be accounted for using multiple imputation methods, including Multiple Imputation by Chained Equations (MICE). In qualitative variables, the estimated sample size is deemed adequate with respect to anticipated information-richness to perform a thematic analysis.

